### Who will solicit informed consent? {26a}

Consent procedures were approved by the Domain Specific Review Board (DSRB) of the National Healthcare Group in Singapore. All potential subjects are required to sign the informed consent in order to participate in the study.

### Additional consent provisions for collection and use of participant data and biological specimens in ancillary studies {26b}

There are no additional consent provisions for collecting or using biological samples. If we decide to do an ancillary study in the future, we will seek prior consent of participants to be re-contacted and re-consent for the ancillary study following DSRB approval.

## Interventions

### Explanation for choice of comparators {6b}

mHealth may provide practical and scalable support to women adopting and maintaining a healthy lifestyle. The effectiveness of mHealth interventions targeting lifestyle behaviours has been demonstrated [31, 34, 37]. More recently, studies have supported that prevention and promotion request more than one pillar, meaning that holistic lifestyle behaviours, such as PA, diet, sleep, and mental well-being, are more effective in parallel [34]. Studies have shown that education alone is insufficient to support individuals in changing their lifestyles, and it is important to incorporate techniques and behavioural strategies that facilitate and measure the effectiveness of the interventions [31, 34, 37]. Therefore, we propose to compare two mHealth interventions, the intervention group (LvL UP App, Happy App, and Oura Ring) and the comparison group (HAPPY App and Oura Ring). The LvL UP App is based on evidence-based strategies and interactive tools developed in Singapore [35]. The HAPPY App is available to every eligible participant (both groups) in the trial; it provides public holistic health recommendations and displays participants’ health data measured during study visits over time. Also, the Oura ring is a sleep tracker that includes heart rate variability, and a step tracker will be provided to both groups.

### Intervention description {11a}

The comparison and intervention group will be assigned to holistic lifestyle mHealth interventions. The comparison group (Happy App and Oura ring) will receive only psychoeducation to promote a healthy lifestyle through the HAPPY App and sleep tracking using an Oura ring and associated App. The Happy App was developed by the Singapore Institute for Clinical Sciences (SICS); it encompasses only educational content on lifestyles based on resources from the Singapore Health Promotion Board, including information about diet intake, physical activity, sleep, and mental well-being. The HAPPY app also displays health outcome data collected during the study visits (e.g. body weight, blood pressure, fasting glucose, and 2-h 75 g OGTT). The Oura Ring is an activity-tracking wearable that monitors physical activity, sleep, and heart rate variability, which can be synced with the Oura App.

The intervention group (LvL UP App, Happy App, and Oura Ring) will receive the same Happy App, Oura Ring and Oura App, with the additional LvL UP App version 2.0. The LvL UP App has been developed by the Future Health Technologies Programme at the Singapore ETH-Centre (SEC) for iOS and Android. It is designed to be culturally relevant in Singapore and is based on evidence-based behavioural strategies [35]. A separate paper[35] describes the conceptual model, development process, and characteristics of LvLUP version 1.0. In this study, we will use an updated 2.0. version. The LvL UP App 2.0 is a smartphone-delivered holistic lifestyle intervention focusing on three core pillars: *eat well* (diet), *move more* (PA), and *stress less* (mental well-being), including sleep content in each pillar delivered through a coaching health and tools paradigm.

#### LvL UP App: coaching health

The participants assigned to LvL UP will receive weekly motivational interview-inspired coaching sessions from a digital coach (conversational agent; CA) on topics related to the core intervention pillars. Coaching sessions are text-based dialogues between the participant and the CA based on predefined rules, and each session lasts between pillars, which are recommended in a predefined order, although participants can choose the order and topic if they wish. There are eight coaching sessions per pillar, which are recommended in a predefined order, although participants can choose the order and topic if they wish. The participant starts the intervention with a welcome dialogue, which introduces the LvL UP App and assesses the participant’s needs in each of the core pillars using the Patient Health Questionnaire-4 (PHQ-4) [38], a Modified Food Frequency Questionnaire (FFQ) based on dietary recommendations, and the International Physical Activity Questionnaire-Short Form (IPAQ-SF) [39]. Based on the participant’s needs, a starting pillar is recommended, but the participant can still choose the pillar they wish to focus on. Following the welcome dialogue, the participants complete two short sessions to identify their perceived values and strengths, which are later reflected to the participant by the CA during coaching sessions.

#### LvL UP App: tools

Additionally, the LvL UP App includes different tools that complement each pillar, including a set of self-regulatory behaviour change techniques, actionable habit-forming suggestions, and a slow-paced breathing training mini-game. The self-regulatory tools include a low-burden image tracking food diary (*MakanMemo*), a step tracker (*StepLah!*) that displays steps collected by Apple Health (iOS) or GoogleFit (Android) and allows users to set and track step goals, including brisk steps (120 steps/min or higher), and a *Journal* with different templates inspired by cognitive behavioural therapy to support mental well-being. Life Hacks are actionable tips for improving healthy habits and are designed to be easily executed during the daily routine. They operate on the premise that taking small, concrete actions can accumulate and lead to noticeable changes over time. Finally, Breeze is a slow-paced breathing training mini-game that uses breathing data collected by the smartphone microphone to move a sailboat along a river in real time [40].

The intended use of the LvL UP intervention is to complete weekly coaching sessions and use the tools daily. Gamification is built into the App whereby a puzzle piece is awarded for completed activities to fill up the LvL UP Shield. Once the shield is filled, the participant progresses to the next level and the shield resets. There are three levels in total. The LvL UP App delivers reminders and prompts (push notifications) related to intervention actions to encourage the participant to complete the intervention as intended.

### Criteria for discontinuing or modifying allocated interventions {11b}

The participant will be withdrawn from the study if she becomes pregnant during the 1-year intervention period. If a participant becomes pregnant during the 3-year follow-up period, she will skip the follow-up visit for the year and return to the subsequent follow-up visit(s) post-pregnancy. In the same way, if a participant is diagnosed with T2D by her doctor during the 1-year intervention period, she will be invited to complete the endpoint study visit measures before being withdrawn from the study. If the participant is diagnosed with T2D by the study team during the follow-up visits, she will be removed after completing that visit.

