### Outcomes {12}

Table 1 shows the outcomes and timeline of the study. The primary outcome will be the onset of T2D/confirmed by a 2-h 75 g oral glucose tolerance test (OGTT) over a 4-year study period. OGTT will be done at the screening visit, year 1 visit, and follow-up visits in years 2, 3, and 4. Secondary outcomes include (a) onset of impaired fasting glucose and impaired glucose tolerance; (b) changes in cardiometabolic variables (body weight, HbA_1c_, insulin, blood lipids, blood pressure), and (c) changes in women’s body composition as assessed by bioelectrical impedance analysis (BIA). Secondary measures will be taken at baseline visits, middle point, year 1, and 2, 3, and 4-year follow-up period.

**Table 1 Tab1:** Outcomes and timeline

Assessments	Screening visit	Baseline visit	Midpoint visit (26/27 weeks)	Year 1 visit	Year 2 visit (follow-up)	Year 3 visit (follow-up)	Year 4 visit (follow-up) endpoint
Lab tests							
OGTT test	X				X	X	X
Height, weight and blood pressure measurements	X	X	X	X	X	X	X
Bio-sample collection: buccal swab, saliva, and stool samples		X		X			X
BIA		X		X	X	X	X
Fasting blood draw		X	X	X	X	X	X
Questionnaires							
Demographics	X			X			
GDM and family history of diabetes	X						
Spouse and child health	X			X			
Lifestyle and dietary	X			X			
Diabetes awareness	X			X			
14-day e-Diary recording		X	X	X	X	X	X
SF-36		X	X	X	X	X	X
STAI		X	X	X	X	X	X
BDI-II		X	X	X	X	X	X
CERQ		X	X	X	X	X	X
MEQ		X	X	X	X	X	X
PSQI		X	X	X	X	X	X
SHS		X	X	X	X	X	X
HLQ		X	X	X	X	X	X
PSS-4		X	X	X	X	X	X
WHO-5		X	X	X	X	X	X
Child-related questionnaires							
BISQ-R-SF		X		X			
CSHQ		X		X			
StimQ toddler/preschool		X		X	X	X	X
ASQ-3		X		X	X	X	X
BRIEF-2		X		X	X	X	X
BASC-3-BESS Parent Form		X		X	X	X	X
Questionnaires administrated within the LvLUP App (intervention group only)							
PHQ-4		x	x				
IPAQ-SF		x	x				
MFFQ		x	x				

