### Sample size {14}

#### Expected number of participants

The sample size is estimated based on the cumulative diabetes risk identified from the GUSTO study [12]. We assume groups of equal size, with a significance level of 0.05% and a power of 80%. Additionally, we consider a median survival time of 6 years for the non-intervention group (based on GUSTO data), a follow-up period of 3 years, and an expected 50% reduction in the risk of developing T2D for the intervention group (hazard ratio = 0.5). These assumptions yield a cumulative event rate of 0.22 for the comparison group and 0.12 for the intervention group. Considering a 20% censoring rate, we calculate a sample size of 189 for the intervention group and 188 for the comparison group, aiming for a total of 65 events over the study period[63].

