Biological samples will be collected through blood tests, which will be analyzed by an accredited lab providing the normal reference range of the lab results. The PI ([name]) will review blood test results. For all abnormal blood test results and incidental findings discovered during the study period, the study PI will determine if the findings are clinically significant and actionable. The study PI will sign a referral letter to seek primary healthcare. Subsequently, a delegated study team member will contact the participant to relay the internal findings on behalf of the study PI. Participants who agree to be re-identified and notified of the internal findings will be contacted at their primary contact number provided in the consent form. The referral letter will be emailed to her. If the participant is uncontactable on her direct contact number, her next of kin listed on the consent form will be contacted. If the participant and next of kin are not contactable after 1 month, the referral letter will be sent directly to the participant’s home address. In the case incidental findings meet the study exclusion criteria, the affected participant will be informed and withdrawn from the study.

For the rest of the study measures/questionnaires, there is no clinical validation available. Hence no applicable management plan will be carried out.

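### The primary event requires OGTT confirmation, but two withdrawal rules can remove a woman found to have T2D without an OGTT, and the protocol does not say how she counts

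*Protocol article*

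**What the plan says.** All references are to the Protocol article.

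- **Event definition, Outcomes {12}:** "The primary outcome will be the onset of T2D/confirmed by a 2-h 75 g oral glucose tolerance test (OGTT) over a 4-year study period". HbA1c, fasting glucose, a medical record and treatment are not named as alternative confirmation.
- **OGTT schedule, Outcomes {12}, text:** "OGTT will be done at the screening visit, year 1 visit, and follow-up visits in years 2, 3, and 4".
- **OGTT schedule, Table 1:** the row reads "OGTT test X X X X". The four marks stand under screening and years 2, 3 and 4. The year 1 and midpoint cells are empty. The last column is headed "Year 4 visit (follow-up) endpoint".
- **Doctor's diagnosis in year 1, section {11b}:** "if a participant is diagnosed with T2D by her doctor during the 1-year intervention period, she will be invited to complete the endpoint study visit". After that she is withdrawn.
- **Years 2 to 4, section {11b}:** "If the participant is diagnosed with T2D by the study team during the follow-up visits, she will be removed after completing that visit". A doctor's diagnosis in these years is not mentioned.
- **Abnormal bloods, section {22}:** for results judged clinically significant, "The study PI will sign a referral letter to seek primary healthcare". The section adds that a woman whose incidental findings meet an exclusion criterion is withdrawn. Diabetes is exclusion (a) in Eligibility criteria {10}.
- **Other treatment, section {11d}:** concomitant drug treatment is allowed and is to be assessed during follow-up.

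**The concern.** The protocol foresees T2D coming to light in ways other than an OGTT, and in two of them it withdraws the woman. It does not say whether such a case is a primary event. If the definition is applied as written, a woman who has the outcome but no OGTT does not count, and her follow-up stops because she has the outcome. Treating her as censored makes the censoring informative; treating her as event-free misclassifies her. Either way the T2D rate is understated.

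The loss need not be equal between arms. Participants and staff are unblinded (section {17a}), and section {11c} gives calls, texts and SMS prompts to the LvL UP arm, while the HAPPY App has only its own reminder. Clinical detection, or acceptance of the offered visit, could therefore differ by arm.

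**Working it through.** **Routes to a diagnosis, followed through the text**

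1. *Doctor's diagnosis in year 1.* The woman may decline the invitation, and then there is no OGTT from this trial. If she accepts and the year 1 visit is meant, the {12} text gives her an OGTT and Table 1 does not. If the year 4 visit is meant, as the Table 1 label suggests, Table 1 marks an OGTT, but it is not stated when that set of measures would be taken.
2. *Abnormal fasting bloods under {22}.* Table 1 has a fasting draw at the midpoint visit and no OGTT there. If the result is taken to meet the diabetes exclusion, she is referred and withdrawn, and no OGTT is called for.
3. *Doctor's diagnosis in years 2 to 4.* No rule withdraws her, so she stays on the OGTT schedule. Her next OGTT may be taken on treatment, which {11d} permits, and could then be non-diabetic.
4. *Study-team diagnosis at a follow-up visit.* That visit has an OGTT, so the event is captured.

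Routes 1 and 2 can end without a qualifying OGTT; route 3 may.

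**Reproducing the plan's figures**

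Inputs from Sample size {14}: hazard ratio 0.5, control median 6 years, 3 years of follow-up, 20% censoring, 65 events, 189 + 188 = 377 women. The level is printed as "with a significance level of 0.05% and a power of 80" per cent. Taken literally, 0.05% would need 156 events, so I use two-sided 5%.

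- Events (Schoenfeld): (1.960 + 0.842)² / (0.25 × (ln 0.5)²) = 65.3. Power with 65 events is 79.8%.
- Hazards: comparison ln 2 / 6 = 0.1155 per year; intervention 0.0578. With a censoring hazard c of 0.2 per year, the event probability by time T is h/(h + c) × (1 − exp(−(h + c)T)). At T = 3 this gives 0.224 and 0.121, matching the stated 0.22 and 0.12. The mean is 0.1724, and 65 / 0.1724 = 377.

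The plan's figures reproduce.

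**Events arising in year 1**

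The same formula at T = 1 gives 0.0991 × 188 = 18.6 and 0.0509 × 189 = 9.6, together about 28 of 65 (43%). These are all T2D onsets in year 1, not doctor diagnoses, so 28 is a ceiling for the year-1 loss on this model.

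**What a loss would cost**

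The share lost is my assumption. Loss is taken as proportional in both arms, so the hazard ratio stays at 0.5. Power = Φ(√(0.25 × events) × 0.693 − 1.960).

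| Assumed loss | Events left of 65 | Power |
|---|---|---|
| none | 65 | 80% |
| 10% of all events | 58.5 | 76% |
| 20% of all events | 52 | 71% |
| a quarter of year-1 events | 57.9 | 75% |
| half of year-1 events | 50.9 | 70% |

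The starting number matters. The trial plans 400 women and an outcome over 4 years. With 200 per arm and T = 4, expected events are about 81 with the censoring hazard of 0.2 per year, or about 104 if 20% is the total censored by year 4. From 81, a 10% loss leaves about 73 events (84%) and a 20% loss about 65 (80%).

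**The case against.** A reader might infer more than the documents support, in four ways.

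- *That these women are in fact scored event-free or censored.* No section prints a scoring rule. The analysis plan is not shown and may count clinical diagnoses. The literal definition points that way, but it remains an inference.
- *That only a study OGTT counts.* Outcomes {12} does not say so. An OGTT ordered by the woman's doctor could qualify, although nothing provides for obtaining it.
- *That there is never an OGTT at the offered visit, or no route at all in years 2 to 4.* The {12} text lists a year-1 OGTT, so a woman who accepts may well be captured. In years 2 to 4 a doctor's diagnosis does not lead to withdrawal, and {11d} says treatment will be assessed.
- *That power certainly drops.* It does from 65 events. On the 4-year expectation for 400 women, moderate losses leave the target intact.

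It is also fair that a standardised OGTT endpoint is a defensible choice in an open-label trial, that blood draws and referrals follow the same schedule in both arms, and that the screening surveys repeated at year 1 cover medical conditions and recent glucose tests.

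All of this narrows the point without removing it. The event definition and the withdrawal rules are protocol matters and do not fit together as written. A later analysis plan cannot recover a dated result that was not collected before a woman was withdrawn.

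**Conclusion.** The point holds as a mismatch between stated rules. The primary event needs an OGTT, sections {11b} and {22} can end follow-up at the diagnosis without one, and the protocol does not say whether such a woman has had the event. Events can then be lost and censoring tied to the outcome.

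The size cannot be found from the documents. About 28 of 65 planned events arise in the year covered by the {11b} doctor-diagnosis rule. On assumed losses of 10% to 20%, power is about 76% to 71% from 65 events, or still about 80% or better from 81. These figures rest on the exponential model in Sample size {14}, two-sided 5%, equal proportional loss in both arms and a time-to-event analysis; section {20a} names linear mixed models for the primary outcome. A loss that differed by arm would bias the comparison as well, and the documents give no basis for sizing that. The change should be made because it is cheap and protects the main outcome.

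**What to change.** 1. Reconcile {11b}, {12} (text and Table 1) and {22}: which visit the invitation means, whether it includes an OGTT, whether year 1 has one, and what is recorded when abnormal bloods lead to withdrawal.
2. Use one event definition throughout: the first of a diabetic-range OGTT or a doctor's T2D diagnosis supported by a dated laboratory result or medical record, from randomisation to year 4. The date of that result or diagnosis is the event date.
3. Record such diagnoses before any withdrawal and ask about them at every existing visit, including for doctor diagnoses in years 2 to 4.
4. Report OGTT-confirmed T2D alone as a sensitivity analysis.

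The cost is outcome wording, one question and a copy of the result at contacts already planned. The downside is that clinical diagnoses are less standardised and their detection could differ between open-label arms. The documentation requirement limits this, and the OGTT-only analysis shows whether it matters.

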### Eligibility criteria {10}

All eligible females in this study will be (a) women between 21 and 45 years old; (b) with a history of GDM (at least 1 year and no more than 10 years); (c) Chinese, Malay, or Indian ethnicity; (d) BMI between 18.5 and 35 kg/m^2^; (e) not planning to conceive in the next 1 year; (f) not performing exclusive breastfeeding during the study period; (g) owners of a smartphone compatible with the study mobile Apps; (h) proficient in the English language; (j)willing to comply with study protocol; and (k) able to provide written informed consent.

Exclusion criteria include (a) current or previous diagnosis of diabetes (type 1 or 2), except GDM; (b) currently pregnant; (c)given birth within the last 12 weeks; (d) severely limited mobility (e.g. wheelchair-bound, require long-term walking aid, etc.); (e) diagnosed with malnutrition or eating disorder; (f) diagnosed with cancers, unstable heart diseases, severe kidney disease, severe liver disease; (g) diagnosed with severe insomnia, unstable mental conditions, dementia, or cognitive impairment; (h) experienced alcohol or drug abuse; (i) currently having medications known to influence glucose metabolism (e.g. peroral corticosteroids); and (j) currently participating in a concurrent clinical trial or lifestyle intervention study.

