### Methods in analysis to handle protocol non-adherence and any statistical methods to handle missing data {20c}

Intention-to-treat analysis will be used to examine trial efficacy. Total scores will be modelled using fixed effects of time, intervention group, interaction between time and intervention group, and a random effect of individual.

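### Withdrawal rules end outcome follow-up after year-1 pregnancy, T2D or a disqualifying finding, which undermines the ITT analysis and selects later secondary data on the outcome

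*Protocol article*

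**What the plan says.** All references are to the protocol article.

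- **Outcome.** Outcomes {12}: "The primary outcome will be the onset of T2D/confirmed by a 2-h 75 g oral glucose tolerance test (OGTT) over a 4-year study period". Secondary measures run to year 4. On testing, the text says "OGTT will be done at the screening visit, year 1 visit, and follow-up visits in years 2, 3, and 4", but Table 1 has no OGTT mark at year 1.
- **Pregnancy.** Section {11b}: "The participant will be withdrawn from the study if she becomes pregnant during the 1-year intervention period". In the later follow-up period, by contrast, "she will skip the follow-up visit for the year and return to the subsequent follow-up visit(s) post-pregnancy".
- **T2D.** Section {11b} has two rules. A woman diagnosed by her own doctor in year 1 is invited to the endpoint visit and then withdrawn from the study. For the later visits: "If the participant is diagnosed with T2D by the study team during the follow-up visits, she will be removed after completing that visit".
- **Incidental findings.** Section {22}: "In the case incidental findings meet the study exclusion criteria, the affected participant will be informed and withdrawn from the study". The first exclusion criterion in {10} is "current or previous diagnosis of diabetes (type 1 or 2), except GDM".
- **Analysis.** Section {20c}: "Intention-to-treat analysis will be used to examine trial efficacy". Section {20a} also invokes intention to treat, and plans linear mixed models, GEE and multiple linear regression at the final follow-up.

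Nowhere does the article say that a withdrawn woman stays in outcome follow-up.

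**The concern.** An intention-to-treat analysis needs outcome data on the women randomised, whatever happens to them afterwards. These rules stop data collection because of events after randomisation, and one of those events is the primary outcome itself. Two things are at stake.

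- Some primary events may never be observed, or may be observed without the OGTT confirmation that the outcome definition asks for.
- From year 2 onwards the secondary, mental well-being and child data come from women selected for not having developed T2D. If the intervention works, more women are removed from the comparison arm. Preventing common mental disorders is a stated aim, so these data matter.

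An analysis plan cannot recover data that the protocol says not to collect.

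**Working it through.** **1. Which route loses what**

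| Route | Primary event | Later secondary data |
|---|---|---|
| Pregnancy in year 1 ({11b}) | Any later T2D is unobserved | Lost |
| Pregnancy in years 2–4 ({11b}) | Still observable at later visits | One visit missed |
| Own doctor's T2D diagnosis in year 1 ({11b}) | OGTT confirmation depends on accepting an invitation; Table 1 marks no year-1 OGTT | Lost |
| T2D found by the study team at a follow-up visit ({11b}) | Recorded before removal | Lost |
| Incidental finding meeting an exclusion criterion ({22} with {10}) | If the finding is diabetes, withdrawal with no OGTT or visit completion stated; otherwise later T2D is unobserved | Lost |

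In the fourth row the 1-year intervention period is already over. HAPPY App access aside, follow-up is all that she can be removed from. Onset is a first event, so a time-to-event analysis needs nothing after it. If glucose is instead analysed as a repeated measure in the mixed model of {20a}, her series stops at T2D.

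A diabetic-range result on a midpoint or year-1 study blood test falls under {22} if it counts as incidental. Neither T2D rule in {11b} plainly covers it: one concerns a diagnosis by her own doctor, the other concerns the follow-up visits.

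**2. Reproducing the plan's figures ({14})**

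Inputs: comparison median 6 years, hazard ratio 0.5, 3 years, power 80%, 20% censoring. Alpha is printed as 0.05%, but the event total fits only 0.05, two-sided.

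- Events (Schoenfeld): 4(1.960 + 0.842)² / (ln 0.5)² = 65.3; stated 65.
- Hazards: ln 2 / 6 = 0.1155 and half of that, 0.0578 per year.
- Event rate with censoring hazard 0.2 per year: λ/(λ + 0.2) × [1 − exp(−3(λ + 0.2))] = 0.224 and 0.121; stated 0.22 and 0.12.
- N = 65.3 / 0.172 = 379; stated 189 + 188 = 377.

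**3. How unequal removal for T2D would be**

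T2D by year t without other dropout is 1 − exp(−λt):

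| By year | Comparison | Intervention |
|---|---|---|
| 1 | 10.9% | 5.6% |
| 2 | 20.6% | 10.9% |
| 3 | 29.3% | 15.9% |

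Before the year-4 visit the gap is 29.3 − 15.9 = 13.4 points. With the plan's censoring it is 0.22 − 0.12, or 10 points. Either way, nearly twice as many comparison women leave because of T2D.

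In year 1 the expected numbers are 188 × 0.109 = 20.5 and 189 × 0.056 = 10.6, about 31 women. How many would be diagnosed by their own doctor is not known.

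**4. Power if some events are lost**

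No withdrawal rate is given, so let w be an assumed share of events lost beyond the planned censoring. Events = N × 0.17 × (1 − w); power by Schoenfeld.

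| w | N = 377: events, power | N = 400: events, power |
|---|---|---|
| 0 | 64.1, 79.2% | 68.0, 81.5% |
| 5% | 60.9, 77.2% | 64.6, 79.5% |
| 10% | 57.7, 74.9% | 61.2, 77.4% |
| 20% | 51.3, 69.9% | 54.4, 72.4% |

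**The case against.** Several stronger readings are tempting, and the documents do not support them.

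- **That T2D events are censored because they occurred.** For T2D found at a follow-up visit this is wrong, because she completes the visit and the event is on record. Only the other routes put primary events at risk.
- **That every comparison is selected on the outcome.** The year-1 comparison is largely spared: a woman diagnosed by her doctor in year 1 is invited to the endpoint measures first. The selection bears on years 2 to 4.
- **That the rules contradict ITT.** Intention to treat means analysing women as allocated. Withdrawal does not breach that; it undermines it by creating missing data.
- **That diabetes on a study blood test will be treated as an incidental finding.** The primary endpoint is hardly incidental, {22} mentions abnormal results and incidental findings separately, and {11b} has specific T2D rules. This is fair. But {22} makes no exception for diabetes, so the sections still need reconciling.
- **That the mixed model is badly biased.** If removal depends only on recorded glucose, a correctly specified likelihood-based mixed model can largely recover the glucose effect. This does not rescue a regression at the final visit or an unweighted GEE. Nor does it automatically cover mental well-being or child scores, whose models need not contain the glucose that triggered removal.
- **That power falls materially.** Eligibility requires no plan to conceive within a year, no pregnancy rate is given, and the 20% censoring allowance may absorb part of the loss. That allowance does not cure selection on the outcome.

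**Conclusion.** The point holds in a limited form. Sections {11b} and {22} end study participation after events that follow randomisation, which undermines the ITT analysis.

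- Year-1 pregnancy ends primary follow-up for good, although the plan keeps women who become pregnant later.
- Sections {11b} and {22} conflict for diabetes found on a study test, and a woman diagnosed by her doctor in year 1 may leave without OGTT confirmation.
- T2D found at a follow-up visit costs no primary event, but it removes her later secondary, mental well-being and child data.

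The one size that the plan's figures support is the imbalance in T2D by 3 years: about 29% against 16% without other dropout, or 0.22 against 0.12 with the plan's censoring. It assumes exponential hazards and that the hazard ratio of 0.5 is achieved. The resulting bias and the power loss cannot be computed from the documents; the power table only shows a range for assumed losses. This is a cheap improvement. It does not make the primary comparison invalid.

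**What to change.** Amend {11b} and {22}:

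1. Separate stopping study interventions or procedures, which stays a clinical decision, from leaving outcome follow-up.
2. Keep every randomised woman in the outcome visits already scheduled unless she withdraws consent.
3. Reconcile the year-1 and later pregnancy rules for follow-up, so that year-1 pregnancy does not end follow-up for the primary outcome.
4. Reconcile {11b} with {22}, so that diabetes arising after randomisation is recorded as an outcome event.
5. Count documented physician-diagnosed T2D as a primary event alongside OGTT-confirmed T2D.
6. Continue secondary, mental well-being and child assessments after T2D.

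**Cost.** An amendment and some further visits that are already on the schedule. As a rough upper figure at N = 377 without other dropout, women with T2D by years 1, 2 and 3 number 31.1, 59.4 and 85.1 (the percentages above times 188 and 189). That is about 176 visits in years 2 to 4, or about S$14,000 at the S$80 per visit in {18b}. Women kept after year-1 pregnancy or other findings would add to this.

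**Downside.** Measurements after T2D will reflect any treatment started, so those analyses should be stated as estimating a treatment-policy effect.
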